### Baseline and follow-up oral examinations

All of the baseline and follow-up oral examinations will be conducted in the kindergartens, primarily through careful visual inspection with the aid of a World Health Organization (WHO) CPI probe (405/WHO probe, Otto Leibinger, Mühlheim, Germany) and a disposable front-surface dental mirror with light-emitting diode intraoral illumination (MirrorLite, Kudos Crown Limited, Hong Kong, China).

The six upper anterior teeth will be the studied teeth. They will be cleaned and dried with a gauze sponge before evaluation of their caries status. Caries will be diagnosed at the cavitation level. A surface without any cavitated lesions will be considered sound. The carious lesion will be gently explored with a CPI probe in the lesion’s centre. Great care will be taken to avoid tooth damage during the probing. A carious lesion will be recorded as active if softness is detected upon gentle probing. If the lesion is hard when probing, it will be classified as an arrested caries [16, 17]. The surface of each upper anterior tooth will be recorded as sound or carious (active or arrested). Apart from the studied teeth, the decayed, missing (due to caries) and filled primary tooth (dmft) index will be used to record each child’s caries experience (tooth level). Other tooth statuses, such as tooth discolouration and hypermobility, of all primary teeth will be recorded as well. Oral hygiene status will be measured using the visible plaque index [19]. The buccal and lingual surfaces of six index teeth (55, 51, 63, 71, 75 and 83) will be examined. The same examiner will conduct the follow-up oral examinations every 6 months for 30 months in the kindergartens using the same equipment, procedure and diagnostic criteria as those used in the baseline examination. The intraexaminer agreement on the caries and plaque assessment will be monitored and tested in 10% of the children at each stage of the study.

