### Sample size calculation

The mean number of cavitated teeth of a 3-year-old child was five in our previous study [16]. The mean number of new cavitated caries surfaces found in the 62 children in the SDF group was 0.47 (standard deviation (SD) 0.87), and the mean new cavitated caries surfaces in the 61 children in the NaF group was 0.70 (SD 0.84) at the 30-month review. This difference corresponded to a prevented fraction of 33% more in the SDF group when compared to the NaF group, which is considered clinically significant. With the statistical power set at 0.9 and type I error rate of 5% for a two-sided test, the required sample size would be 292 for each group. Considering a dropout rate of 20%, the total number of children to be recruited at baseline should be 365 in each group. Therefore, a total of 730 children need to be recruited at baseline examination for this trial.

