### Data management

Two people will independently enter the collected data into an Excel file (by double entry) and the data will be compared to minimise data entry errors. A statistician will oversee the data entry, data checking and analysis for this project. The intraexaminer agreement in caries diagnoses at each time point will be assessed using Cohen’s Kappa statistics. This trial will employ an intention-to-treat analysis. A per-protocol analysis will be performed if the number of children who stray from the protocol (for instance, by not adhering to the prescribed 6-month intervention, or by being withdrawn from active treatment) differs between the two groups. In that case, only the patients who complete the entire clinical trial according to the protocol will be counted towards the final results. Sensitivity analysis will also be considered by means of multiple imputations for missing values. The level of statistical significance for all two-sided tests will be set at 0.05. For one-sided tests, the level of statistical significance will be set at 0.025.

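### Intention-to-treat is declared, but the 30-month tests on which the trial is sized would, as written, omit children without a 30-month examination, because imputation is only an optional sensitivity analysis

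*Protocol article*

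**What the plan says.** All references are to the protocol article.

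- **Principle.** Data management: "This trial will employ an intention-to-treat analysis".
- **Missing values.** The same section: "Sensitivity analysis will also be considered by means of multiple imputations for missing values". No other method for a missing 30-month value is named.
- **Per-protocol rule.** The same section provides that, if the number of children departing from the protocol differs between the groups, only those who completed the trial as planned count towards the final results.
- **Exclusion.** Blinding: a child whose parents ask for and receive the treatment allocation is removed from the study.
- **Endpoint and tests.** Outcome measure places the primary outcome at the 30-month examination. Subject-level analysis compares mean new caries by t test and proportions by chi-square test.
- **Sizing.** Sample size calculation works from mean new cavitated surfaces at 30 months and then allows for loss: "Considering a dropout rate of 20%, the total number of children to be recruited at baseline should be 365 in each group".
- **Earlier visits.** Baseline and follow-up oral examinations: "The same examiner will conduct the follow-up oral examinations every 6 months for 30 months in the kindergartens". Surface-level analysis firmly plans a multilevel survival model for interval-censored times to cavitation.

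**The concern.** The outcome accumulates over five follow-up examinations. A child with new cavities at 12 months who then leaves has already shown much of the outcome, yet contributes nothing to a t test on 30-month counts unless the missing count is filled in. The plan makes filling it in optional and places it outside the main analysis. The declared intention-to-treat principle is therefore not carried through to the comparison that the trial is powered for.

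Two stated rules add to this. The completers-only rule is triggered by an imbalance between arms, which is where a completers' comparison is least safe. The exclusion of unblinded children could be linked to the outcome: the Data Availability section says parents receive a report of each follow-up examination, and a parent who learns of new cavities may be more likely to ask which treatment was given. How often this would happen is unknown.

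If leaving or exclusion depends on new caries differently in the two arms, the estimated superiority of SDF is biased, in either direction.

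**Working it through.** **1. The plan's own figures.** Inputs, all from Sample size calculation: "With the statistical power set at 0.9"; "type I error rate of 5% for a two-sided test"; SDF, "in the 62 children in the SDF group was 0.47 (standard deviation (SD) 0.87"); NaF, "in the 61 children in the NaF group was 0.70 (SD 0.84) at the 30-month review".

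- Difference: 0.70 − 0.47 = 0.23.
- Common SD: √((0.87² + 0.84²)/2) = 0.855.
- n per group = 2 × (1.960 + 1.282)² × 0.855²/0.23², which gives 291. The t-based version gives 291.5, so 292. The plan's 292 is reproduced.
- 292/0.8 = 365 per group, 730 in total. Planned loss: 365 − 292 = 73 per group, 146 in all.
- Power for a difference of 0.23 is 90.1% with 292 per group and 95.3% with 365.

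That a two-means formula reproduces 292 shows that the powered quantity is the subject-level 30-month mean difference.

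**2. How far 20% loss can move the result.** If drop-outs in one arm differ from that arm's completers by D surfaces, the arm mean shifts by 0.2 × D. The values of D are assumptions.

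- D = 0.25: shift 0.05, which is 0.05/0.23 = 22% of the target difference.
- D = 1.0: shift 0.20, which is 87%. A D of 1.0 is larger than either arm's mean, so this is the far end of the range.

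**3. Tipping point.** Let completers show 0.47 v 0.70, NaF drop-outs average 0.70 and SDF drop-outs average x. The difference in all randomised children is 0.70 − (0.8 × 0.47 + 0.2x) = 0.324 − 0.2x.

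- Standard error at 365 per group: 0.855 × √(2/365) = 0.0633. Critical difference: 1.96 × 0.0633 = 0.124.
- Significance is lost at x = (0.324 − 0.124)/0.2 = 1.00.
- The whole difference is lost at x = 0.324/0.2 = 1.62.

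**4. Simulation of caries-related drop-out.** Set-up: 365 per arm, gamma-Poisson counts over five visits, true means 0.70 and 0.47, about 20-22% loss. The variance-to-mean ratio was 1.6. This matches the SDF figures (0.87²/0.47 = 1.6) but exceeds the NaF ones (0.84²/0.70 = 1.0). The hazard ratio (HR) for leaving after new caries is an assumption; the documents give no such figure. The table shows the average completers' difference, where the truth is 0.23.

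| HR for leaving | NaF only | SDF only | Both arms |
|---|---|---|---|
| 1 (unrelated) | 0.23 | 0.23 | 0.23 |
| 1.5 | about 0.20 | about 0.26 | about 0.22 |
| 2 | about 0.18 | about 0.27 | about 0.22 |
| 4.5 | about 0.11 | about 0.33 | about 0.20 |

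Within-arm regression imputation from the earlier visits returned about 0.23 in every scenario. With unrelated drop-out its standard error was about 5% smaller than the completers'.

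**5. How much earlier information exists.** If drop-outs left evenly across the five intervals (assumption), their last examinations would be at 0, 6, 12, 18 and 24 months. Then 146 × 4/5 ≈ 117 would have at least one follow-up examination. Their average observed share of the 30 months would be (0 + 6 + 12 + 18 + 24)/5/30 = 40%.

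**The case against.** **The survival analysis uses the earlier visits.** A reader might infer that the trial throws away the 6- to 24-month examinations of children who leave. It does not: the planned interval-censored analysis can count a cavity found at 12 months and censor the child's sound surfaces at the last visit. This stands for the trial as a whole. However, that model estimates time to cavitation per surface, not the 30-month mean difference used for the sample size, so it does not repair the subject-level tests.

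**No sentence restricts the main analysis to completers.** This is correct: the omission is inferred from the endpoint, the tests and the role given to imputation. Nor does the protocol state which analysis is the main one, although the outcome definition and the sample size both point to the subject-level comparison. Missing-data detail can be left to a SAP, but this article does not stay silent: it assigns imputation a sensitivity role and makes it optional.

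**Allowing for 20% drop-out is routine.** A reader might take the step from 292 to 365 as itself contradicting intention-to-treat. It does not; it protects power and defines no analysis set. It only shows how many children may lack the endpoint.

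**The large biases need strong assumptions.** Figures of 0.11 or 0.33 need a 4.5-fold hazard in one arm only, in a trial where children and parents are to be kept blind. At 1.5-fold the shift is about 0.03, and with equal dependence in both arms it stays small. This stands. The simulated imputation also used earlier counts under a tractable model, so it supports the approach without guaranteeing it in real data.

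**Conclusion.** The point holds in a limited form. The protocol declares intention-to-treat, but its subject-level 30-month tests would, as written, leave out up to about 146 of 730 children. Its completers-only rule and its exclusion of unblinded children conflict with the declared principle more directly.

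The size depends on why children leave. If leaving is unrelated to caries, there is no bias and the only loss is precision. If children with new caries leave more often, the bias ranges from about 0.01 (both arms, HR 1.5 to 2) to about 0.12 (NaF only, HR 4.5: 0.23 − 0.11), and can favour either arm. These figures rest on assumed hazard ratios and on the simulation model in the working. The documents do not support saying that the result will be biased, only that the plan does not protect the powered comparison although the data to do so are scheduled. The change should be made. The sample size needs no revision.

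**What to change.** - Name the 30-month subject-level comparison as primary and state that it includes all randomised children in their allocated arm.
- Multiply impute a missing 30-month count within arm, using the 6-, 12-, 18- and 24-month counts, the caries-risk stratum and baseline covariates (dmft, questionnaire items). An equivalent likelihood analysis of the repeated counts would also serve.
- Keep and analyse all data collected before a child is unblinded or withdrawn.
- Make the completer and per-protocol analyses sensitivity analyses, and delete the provision that lets them replace the main result.
- Add a delta-shifted imputation in which drop-outs are assumed to differ from similar completers, by arm, up to the tipping point.

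Cost: revised wording in the protocol or SAP and modest programming. The examinations and baseline questionnaire are already scheduled and multiple imputation is already named. The drawback is reliance on an imputation model, which the completer and delta-shifted analyses are there to test.

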### Data analysis

The statistical software SAS for Windows (SAS Institute Inc., USA) and SPSS for Windows (IBM Corporation, USA) will be used for the data analyses. Statistical analysis will be performed at the subject and tooth surface levels. An interim analysis will be performed at 18-month follow-up.

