### Blinding

In this randomised clinical trial, the examiner, the children and their parents will not be informed about the treatment group allocation throughout the study. Each assigned fluoride treatment will be applied after the oral examination by an independent operator. If parents request the treatment history of their child, unblinding is permissible. An unblinded research assistant will disclose treatment allocation to the parents, and the child will be excluded from the study.

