#### Subject-level analysis

Although the data for the primary outcome may not be normally distributed [16], the distribution of the mean would be normal according to the central limit theorem with a relatively large sample size. At the subject level, the outcome includes the percentage of children with no new caries developed over the study period as well as the mean number of new caries. Chi-square tests will be used to test the between-group differences in the proportion of subjects with new caries development and in the proportion of surfaces with new cavitations; *t* tests will be used to study the between-group differences in the mean number of new caries and in the increases in the numbers of nonvital teeth and of hypermobile teeth across the follow-up examinations. This research will also study if the treatment effects differ by patient characteristics (effect modification); the variables that may modify the treatment effects on the outcome variable include sex, baseline caries experience, treatment group assignment, oral hygiene habits, fluoride agent use, diet habits, snacking habits, dental visit behaviour, parental educational level, family income and family status (single- or both-parent households). As the outcome variable may not be normally distributed, Poisson or negative binomial regression will be considered to study the effect’s modification [21]. Aside from the primary outcome, *t* tests will also be performed to study the treatment’s effects on the number of arrested carious surfaces at the 30-month examination between the two groups.

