## Data Availability

The data sets generated and/or analysed during the current study are available from the corresponding author on reasonable request. The results of each follow-up examination will be shared to each participant by a report to the parents. The interim and final results will be shared to other researchers by publications and presentations in international conferences.

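### The sample size spends the 5% on one 30-month comparison of means, but 0.05 applies to every two-sided test, the 30-month caries tests are unranked, and the 18-month interim has no level of its own

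*Protocol article*

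**What the plan says.** All references are to the Protocol article.

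- **Sample size calculation:** "With the statistical power set at 0.9 and type I error rate of 5% for a two-sided test, the required sample size would be 292" per group. The basis is the mean number of new cavitated surfaces at 30 months in the previous study: 0.47 (SD 0.87) with SDF and 0.70 (SD 0.84) with NaF.
- **Data management:** "The level of statistical significance for all two-sided tests will be set at 0.05", and "For one-sided tests, the level of statistical significance will be set at 0.025". The second is the equivalent one-sided level. Neither sentence makes an exception for an interim look or for supportive tests.
- **Subject-level analysis:** the outcome covers "the percentage of children with no new caries developed over the study period as well as the mean number of new caries". New caries is compared by chi-square on children, by chi-square on surfaces and by a t test on the mean number.
- **Surface-level analysis:** a multilevel survival model for interval-censored data compares time to cavitation between the groups.
- **Data analysis:** "An interim analysis will be performed at 18-month follow-up". The outcome, purpose and level of this analysis are not given.
- **Data Availability:** "The interim and final results will be shared to other researchers by publications and presentations in international conferences". No date is given.
- **Outcome measure** and **Hypothesis:** both place the primary question at 30 months only.
- **Ethical consideration:** the only stopping rule concerns safety.

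**The concern.** The 5% in the sample size belongs to one test at one time. The rest of the plan gives the same 5% to each of several tests of the same question, does not say which of them decides, and adds an earlier look. A reader of the final report could not tell whether superiority rested on the test the trial was sized for or on whichever reached 0.05.

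This matters because the Discussion says a positive result should help change the standard of care. Such a claim should carry the stated error rate. Release of by-arm results before the 30-month examinations would also be a risk to trial conduct, since one examiner scores every visit and parents may ask for their child's allocation.

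**Working it through.** **1. The plan's own figure.** The difference is 0.70 − 0.47 = 0.23. The pooled variance is (0.87² + 0.84²)/2 = 0.731, so the SD is 0.855. Then n = 2 × (1.960 + 1.282)² × 0.731 / 0.23² = 290.5, or 291 per group. The t-test version gives 291.5, so 292. Allowing for dropout, 292/0.80 = 365 per group, 730 in total. The stated size reproduces as one two-sided 5% comparison of means, with no allowance for a second test or look.

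**2. More than one test at 30 months.** Trials with no treatment effect were simulated with 292 children per arm. New surfaces per child followed a negative binomial distribution with mean (0.47 + 0.70)/2 = 0.585 and SD 0.855, so the shape is k = 0.585²/(0.731 − 0.585) = 2.34.

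| 30-month rule for claiming superiority | False-positive risk |
|---|---|
| t test on mean count alone | 5.0% |
| Child-level chi-square alone | 5.0% |
| Either of the two | 7.6% |

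A separate simulation that added a survival model respecting clustering gave 7.8% to 8.0% for any of three valid tests. The increase over 7.6% is small because the tests use the same events and are strongly correlated.

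**3. The surface-level chi-square, kept apart.** Assume four surfaces on each of six teeth, 24 per child. The proportion of surfaces with new caries is 0.585/24 = 0.0244. If surfaces were independent, the variance of a child's count would be 24 × 0.0244 × 0.9756 = 0.571. The planning SDs give 0.731, a ratio of 1.28. The nominal 1.96 then acts as 1.96/√1.28 = 1.73, an error of about 8.3% (8.5% in simulation) for this test on its own. That comes from ignoring clustering, not from testing several times, so it is left out of the multiplicity figures.

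**4. Two looks at one test.** The information at 18 months is not stated. Taking it as 18/30 = 0.6, the correlation between the 18-month and 30-month statistics is √0.6 = 0.775. The chance under the null that either exceeds 1.96 in absolute value comes from the bivariate normal distribution.

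| Assumed information at 18 months | Correlation | Risk with 0.05 at both looks |
|---|---|---|
| 50% | 0.707 | 8.3% |
| 60% | 0.775 | 8.0% |
| 70% | 0.837 | 7.6% |

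These figures apply only if the 18-month result may support a claim or stop the trial. If it can do neither, one pre-named 30-month test keeps exactly 5%.

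**5. The remedy.** With two-sided 0.001 at 18 months (critical value 3.29) and 0.05 at 30 months, the total at 60% information is 0.0501. The final test keeps 0.05, so 292 per group stands.

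**The case against.** **The deciding test can be inferred.** The Hypothesis concerns the number of sound surfaces that cavitate, the sample size uses the mean number of new surfaces, and Subject-level analysis opens by justifying a comparison of means. Together these point to the t test. This is fair, and it makes the fix easy. It does not settle the matter, because the same section puts the percentage of caries-free children beside the mean and ranks neither.

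**An unseen analysis plan may hold the hierarchy and the interim level.** An article need not carry such detail. Here, however, Data management states a rule, 0.05 for all two-sided tests. It may be meant as a general convention, but as worded an analysis plan with a different interim level would contradict it.

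**Stronger readings that a reader might infer, and that the article does not support:**

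- *The primary outcome is tested for efficacy at 18 months.* The article does not say what the interim tests. It defines the primary outcome at 30 months and states no efficacy stop or early claim.
- *Sharing interim results breaks the masking.* The Blinding section says "the examiner, the children and their parents will not be informed about the treatment group allocation throughout the study". Group-level results do not reveal any child's allocation, and no publication date is given, so release before the 30-month examinations is possible but not stated. The possible effect on the examiner or on parents is a precautionary concern.
- *The error rate is 10% to 18%.* Figures that high come largely from the surface-level chi-square's neglect of clustering. The upper ones also use a dispersion of k = 0.77, which implies an SD of √(0.585 + 0.585²/0.77) = 1.01, against 0.84 and 0.87 in the article.

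**Conclusion.** The concern holds in a limited form. The trial is sized for one two-sided 5% test, while the written rules allow 0.05 to each of several unranked tests of new caries and set no separate level for the interim.

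- **Several 30-month tests:** about 8% if any valid one may support superiority, and 7.6% for the t test plus the child-level chi-square. This rests on negative binomial counts matching the planning mean and SDs, and does not depend on the interim.
- **Interim:** about 8% for one test at two looks, with 50% to 70% information assumed, and only if an 18-month result at 0.05 may support a claim.

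The two figures describe separate situations and should not be added. Loss of masking is not shown. The clustering fault in the surface-level chi-square is real but is a separate point.

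**What to change.** 1. Name one confirmatory test: the between-group comparison of the mean number of new cavitated upper-anterior surfaces per child at 30 months, two-sided 0.05. Label every other test of new caries supportive, and limit the sentence on 0.05 in Data management accordingly.
2. State the purpose of the 18-month analysis and that no superiority claim will be made from it. If the arms are compared then, require two-sided p<0.001 for any claim, so that the final test keeps 0.05.
3. As a precaution for trial conduct, withhold by-arm interim results from the examiner and from publication until the last 30-month examination, and say so in Data Availability.

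The cost is wording and a deferred interim paper. No extra children are needed, because the confirmatory test is the one already sized at 292 per group.
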